## Abstract

**Background:**

A sense of loss of control over eating, such that eating occurs despite the intent not to, is common in people with obesity and eating disorders such as binge eating disorder and bulimia nervosa. Currently, options for management of loss of control eating are limited. We recently determined that the pro-drug N-acetylcysteine (NAC) reduces compulsive-like eating in a rat model of diet-induced obesity. We will now conduct a single site, open-label pilot study to examine the feasibility of a randomized controlled trial (RCT) of NAC for loss of control eating in humans.

**Methods:**

Thirty-six adult volunteers with loss of control eating will be enrolled. All participants will receive NAC at a dose of 1200 mg orally twice daily for 12 weeks. Eating behaviors and triggers will be assessed before and after the NAC treatment period using questionnaires (Eating Loss of Control Scale, Palatable Eating Motives Scale: Coping Subscale, Food Craving Inventory, Reward-Based Eating Scale, Perceived Stress Scale, and Emotional Eating Scale) and ecological momentary assessment (EMA). The primary outcomes of this feasibility study are recruitment rate, participant retention rate at week 12, and medication adherence. The secondary outcome is change in Eating Loss of Control Scale score from baseline to week 12. Exploratory data will be collected on the change in eating behaviors from baseline to week 12. Although EMA can provide real-time data on eating behaviors compared with retrospective questionnaires, it relies on repeated daily measurement for long periods which can affect participant’s adherence to study protocol. Therefore, this feasibility study will assess the performance of EMA versus retrospective questionnaires and will determine which approach suits the purposes of the research.

**Discussion:**

The results of this study will inform the feasibility of a RCT of NAC for loss of control eating using EMA.

**Trial registration:**

This study was prospectively registered with the Australian and New Zealand Clinical Trials Registry in June 2022 (ACTRN12622000902796).

## Introduction

### Background

Eating behavior is controlled by both homeostatic and non-homeostatic processes. For some people, however, eating behavior is not always driven by homeostatic need and can become compulsive in nature [1]. People with compulsive eating experience a sense of loss of control over their eating behavior, i.e., eating despite the intent or desire not to and find it difficult to stop eating [1, 2]. This eating is often habitual (e.g., mindless eating) and occurs in response to emotional triggers (e.g., when feeling angry, down, bored, or stressed), food-associated cues (e.g., the smell or sight of food), and contexts (e.g., celebratory events). They also tend to think about food a lot (preoccupation, colloquially known as “food noise”), and they may frequently experience cravings for certain foods [1–3]. Though not a clinical diagnosis, loss of control eating can have a negative impact on health and on the outcomes of behavioral, medical, and surgical obesity treatment [4–7]. Loss of control eating is found in both children and adult with 42–55% of children aged 8–13 years old and 21–33% of men and women reporting episodes of loss of control eating [1].

Compulsive eating is a common feature of obesity and eating disorders (such as binge eating disorder and bulimia nervosa [8]); hence, treatment for compulsive eating may potentially offer shared therapeutic benefits for these conditions. However, treatment options targeting this behavior are limited. Psychological intervention such as cognitive behavioral therapy (CBT) is considered the first line of treatment [9]. Currently, there is only one medication approved for the treatment of any form of compulsive eating and that is lisdexamfetamine, a stimulant which is FDA-approved for binge eating disorder. However, being an amphetamine medication, lisdexamfetamine comes with a risk of abuse [10]. Further, cardiovascular side effects including palpitations and increased blood pressure have been reported, as well as sleep disturbances. These undesirable effects contribute to medication discontinuation and can represent a challenge for the wider use of this drug [9]. Stimulant medications may improve compulsive eating through their dual effects on reward and executive function. Stimulants increase the availability of catecholamine to improve executive function. They also act on the reward system to suppress appetite which is associated with increased extracellular level of dopamine in the nucleus accumbens [11]. Several medications, such as antidepressants (e.g., fluoxetine), anticonvulsants (e.g., topiramate), and opioid antagonists (e.g., naltrexone) have been proposed as potential candidates for the treatment of compulsive eating [10, 11], though further research is needed to establish their efficacy for this purpose. Many pharmacotherapies used in clinical trials for compulsive eating have not shown high efficacy in reducing symptomatology (e.g., the frequency of binge eating), and the wider use of some of these drugs is limited by their adverse effects [11]. Findings from RCT testing antidepressant drugs including fluvoxamine, duloxetine, buproprion, and desipramine either given as monotherapy or in combination with other intervention (e.g., CBT) have failed to significantly improve binge eating outcome [12]. The anticonvulsant, topiramate, has been shown to reduce binge eating compared to placebo [12–14] and enhance CBT outcomes for binge eating [15]. However, the wider use of topiramate is limited by its high rates of adverse effects and dropout rates (26–68% dropout) [11] suggesting that further investigation of potential pharmacotherapies for compulsive eating is warranted. Based on neuropharmacological systems involved in compulsive eating, several pharmacotherapy options have been investigated including medications that target the cholinergic system, orexin system, glutamatergic system, trace amine-associated receptor-1, cannabinoid receptor 1, and the sigma-1 receptor [2].

There are several lines of evidence to suggest that N-acetylcysteine (NAC) could be of potential benefit for compulsive eating. NAC, a cysteine prodrug, has been shown to reduce several compulsive behaviours, such as use of addictive drugs and compulsive hair pulling and skin picking [16]. Abnormal regulation of glutamate in the striatum has been implicated in the pathophysiology underlying compulsive behaviors [17, 18]. Therefore, the mechanism of action of NAC may involve modulation of the cysteine-glutamate antiporter, known as system xc-, and the glial glutamate transporter, GLT-1, which play a key role in glutamate homeostasis and influence glutamate transmission [19]. Repeated use of drugs of abuse such as cocaine leads to persistent reduction of cysteine-glutamate exchange via system xc- in brain areas involved in hedonic motivated behaviour such as the nucleus accumbens [20–23] which disrupts the level of extracellular glutamate. Similarly, drugs of abuse also reduce the expression of GLT-1 in the nucleus accumbens [20, 21]. Administration of NAC restores xc-function and ameliorates drug-seeking behavior [23–25]. Likewise, NAC administration upregulates GLT-1 expression [21, 26] which mediates NAC inhibition of cue-induced reinstatement of cocaine seeking [26]. Restoring extracellular glutamate with NAC has been shown to inhibit excitatory synaptic activity in the nucleus accumbens via activation of group II metabotropic glutamate receptors (mGluR2/3) [27]. In humans, NAC treatment at 2400 mg/day for 4 weeks reduces tobacco use (32 participants in total) [20] and cocaine use (23 participants in total) [28]. Our laboratory has shown that NAC reduces compulsive eating behaviour in diet-induced obese rats [29]. NAC has also been shown to reduce binge-like eating in a model where rats were given daily limited access (30 min) to a highly palatable diet [30] and reduce food-seeking behavior in a rat model of cue-induced reinstatement [31]. As yet, there are no studies examining the effect of NAC on compulsive eating in humans. One small study has examined the effects of NAC on eating behavior in people with bulimia nervosa [32]. This open-label study examined the effect of NAC on binge-purge frequency in eight participants, of whom only two completed the 12-week intervention (the following reasons for attrition were reported: loss to follow up, lack of efficacy, or experiencing side effects [32], thus limiting the conclusions that can be drawn. Therefore, more research is required to evaluate the efficacy of NAC for compulsive eating.

Here, we are conducting a pilot study to explore the utility of NAC for the treatment of loss of control eating. We will employ ecological momentary assessment (EMA) to monitor treatment response. EMA can capture valuable real-time information on eating behaviors compared with retrospective questionnaires but requires more resources and time commitment for data collection. Therefore, this feasibility study will assess whether this approach suits the purposes of the research.

### Aims

The primary aim of this study is to assess the feasibility of delivering a 12-week NAC intervention in people with loss of control eating. The secondary objective is to estimate the clinical efficacy of NAC to inform a sample size calculation for future research. In addition, we aim to explore the performance of self-reported measures of eating behaviors and mood using EMA compared with retrospective questionnaires.

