## Methods/design

### Design

This is an open-label single-arm pilot study to examine the feasibility of recruiting and retaining participants during a 12-week NAC intervention in people with loss of control eating. After completing the baseline assessments, all participants will receive NAC orally at a daily dose of 2400 mg (two capsules of 600 mg, twice daily) for 12 weeks. A follow up assessment will be conducted after treatment using the same measures as in the baseline assessment. The trial flow diagram (Fig. 1) depicts the overall procedure in the study. This single-site study will be conducted at the Florey Institute of Neuroscience and Mental Health, Melbourne, Victoria, Australia.

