### Outcome measures

The primary outcomes are participant retention rate, recruitment rate, and medication adherence. Retention rate will be calculated as the proportion of individuals who completed retrospective questionnaires at week 12. Recruitment rate will be assessed by calculating the number of recruited participants per month. Adherence to medication will be the percentage of doses taken, based on capsule count. The secondary outcome is change in Eating Loss of Control Scale score from baseline to week 12. The exploratory outcomes include the following:Adherence with EMA protocol (percentage of EMA surveys completed; percentage of participants who completed at least 80% of EMA surveys);Concordance between EMA and retrospective measures (internal consistency, convergent validity, and sensitivity to detect treatment outcome);Change of scores in the drivers of eating and eating behaviour from baseline to week 12:Emotional eating (Palatable Eating Motives Scale: Coping subscale and Emotional Eating Scale);Food craving (Food Craving Inventory);Preoccupation with food (Reward-based Eating Scale);Perceived stress (Perceived Stress Scale).

The outcomes will be assessed using both retrospective questionnaires (described below) and EMA.

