### Handling of missing data

Participants with missing data on post-intervention outcome assessment (retrospective questionnaire) will be excluded from analysis.

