### Statistical analysis

All participants who received at least the first dose of study drug and provided at least 1 post baseline assessment will be included in the analysis. Data will be cleaned and checked for accuracy. Demographic characteristics will be summarized as proportions for categorical data and means and standard deviations for continuous data or medians as appropriate. For primary outcomes, retention rate will be calculated as the proportion of individuals who completed retrospective questionnaires at week 12; recruitment rate will be calculated as the total number of participants recruited divided by the total number of months that the trial recruited for. Secondary and exploratory outcomes will be reported as estimates of effects (95% confidence interval). Pearson or Spearman correlation will be used to analyze the concordance between EMA and retrospective measures (convergent validity), and reliability (internal consistency) will be examined with Cronbach’s alpha. Compliance rate will be estimated from the average number of EMA surveys completed out of all administered surveys.

Adverse events will be reported as the number and percentage of participants reporting adverse events. Other information about each adverse event including start date, stop date, severity, relationship, expectedness, outcome, and duration, including adverse events leading to premature discontinuation from the trial intervention and serious treatment-emergent adverse events, will also be collected.

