This study has some limitations. Firstly, we do not exclude people who use drugs that may affect appetite and eating behaviors, such as topiramate, as the primary goal of this pilot study is to determine the feasibility of delivering a 12-week intervention of NAC with a 7-day EMA assessment delivered 3x daily during this intervention. Medications with demonstrated effects on compulsive eating behaviours (such as lisdexamfetamine) will be excluded from a subsequent phase 3 trial examining the efficacy of NAC. Secondly, our definition of loss of control eating is more inclusive and does not satisfy the criteria for an eating disorder diagnosis. However, a low level of inclusion criterion (i.e., 1–2 episodes per month) is used by other studies when trialling possible interventions for compulsive eating [34–37]. Thus, our definition is consistent with other studies. Thirdly, we conducted an open label study with no control arm. Uncontrolled trials can produce greater estimates of the mean treatment effect; thus, they may inflate the expectations from the intervention. Due to this potential bias, efficacy results from uncontrolled trials are not as valid as RCTs and have limited generalizability [63, 64]. However, in this pilot study, our focus is not evaluating the efficacy of N-acetylcysteine. Instead, we are evaluating the feasibility of delivering the intervention and adherence to the intervention and assessments. This information is critical for designing a future RCT to empirically determine the efficacy of N-acetylcysteine for the treatment of compulsive eating. Hence, a single-arm design is appropriate for this purpose. This design is pragmatic and allows for smaller sample size. Fourthly, the use of self-reported data for assessment of certain outcomes may introduce potential measurement bias (e.g., for eating behavior).

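### The secondary objective assigns an uncontrolled before-after change the job of an efficacy estimate for sizing a future trial, a job that this design cannot do and that the protocol's own limitations argue against

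*Protocol article*

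**What the plan says.** Aims, protocol article: "The secondary objective is to estimate the clinical efficacy of NAC to inform a sample size calculation for future research".

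Design: "This is an open-label single-arm pilot study to examine the feasibility of recruiting and retaining participants during a 12-week NAC intervention". There is no control arm.

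Outcome measures: "The secondary outcome is change in Eating Loss of Control Scale score from baseline to week 12". This is the only secondary outcome.

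Statistical analysis: "Secondary and exploratory outcomes will be reported as estimates of effects (95% confidence interval"). Handling of missing data: "Participants with missing data on post-intervention outcome assessment (retrospective questionnaire) will be excluded from analysis".

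The limitations paragraph of the Discussion says: "Uncontrolled trials can produce greater estimates of the mean treatment effect; thus, they may inflate the expectations from the intervention". It then defends the single arm on the ground that "in this pilot study, our focus is not evaluating the efficacy of N-acetylcysteine".

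The article gives no effect size, standard deviation or sample size for the future RCT. It does not say how the efficacy estimate would enter that calculation.

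**The concern.** A two-arm RCT is sized on the difference between NAC and its control, together with a standard deviation. A single-arm change is a different quantity. Besides any drug effect it can contain:

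- placebo response and expectancy, since treatment is open label and the outcome is self-reported;
- the effect of the weekly contact described under Intervention, which both arms of an RCT could share;
- some regression to the mean, since entry requires a recent episode assessed on the outcome scale;
- selection, since people without the final questionnaire are left out. The Introduction reports that lack of efficacy was one reason for dropout in an earlier small NAC study.

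Most of these would be expected to enlarge the apparent benefit. The planned 95% CI describes sampling error and none of these biases.

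At stake is the pilot's use in designing the RCT. The objective names clinical efficacy as the input to sizing, and nothing in the article narrows this to variability. A later team could take the mean change as the target difference and cite the protocol for doing so.

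**Working it through.** **1. The plan's own figure.** The only sample size stated is 36, under Sample size estimation: retention 80% against 60%, 80% power, p < 0.05, exact binomial. With one-sided alpha 0.05 and success at 27 or more retained out of 36:

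- P(X ≥ 27 | 36, 0.60) = 0.0449
- P(X ≥ 27 | 36, 0.80) = 0.832

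This is the smallest n that meets both limits, so 36 reproduces. It rests on retention alone and the present point does not touch it.

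**2. What the single-arm change estimates.** Write the expected change on NAC as Δ = δ + ν, where δ is the difference from control that the RCT would estimate and ν is the change that would also occur on control. One arm identifies Δ only. With f = ν/Δ, δ = (1 − f)Δ, and nothing in this design estimates f.

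**3. Consequence if Δ were used as δ.** No input here comes from the documents except the completer count in step 4. *Assumptions:* standardised change D = 0.5 (mean change divided by the SD of change); 1:1 RCT analysed on change scores with the same SD; two-sided 5%; 80% power; two-sample t-test. This gives 64 per arm. The true standardised difference is then D(1 − f):

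| f (assumed) | True difference | Power with 64 per arm | Needed per arm | 1/(1 − f)² |
|---|---|---|---|---|
| 0 | 0.500 | 80% | 64 | 1.0 |
| 25% | 0.375 | 56% | 113 | 1.8 |
| 50% | 0.250 | 29% | 253 | 4.0 |
| 75% | 0.125 | 11% | 1,006 | 16.0 |

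Required n varies as 1/d², so the multiplier 1/(1 − f)² holds approximately for any D. Starting from D = 0.8 or 1.0, the powers are again about 56%, 29% and 11%.

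**4. Precision.** Expected completers: 0.80 × 36 = 28.8, taken as 29. For an observed D = 0.5, t = 0.5 × √29 = 2.69 on 28 degrees of freedom. Inverting the noncentral t distribution gives a 95% CI for the standardised change of 0.109 to 0.883. Carried into the same calculation, these limits give 1,312 and 22 per arm. The spread runs both ways, so it shows imprecision and not a shortfall.

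**5. What the pilot can supply.** The 95% CI for an SD at n = 29 uses chi-square quantiles on 28 degrees of freedom, 44.46 and 15.31:

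- lower limit: √(28/44.46) = 0.79 times the estimate
- upper limit: √(28/15.31) = 1.35 times the estimate

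This interval is wide but usable, and a shift in the mean that is common to everyone does not alter it.

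**The case against.** The article is candid about its design. The Discussion names the missing control arm, says that efficacy results from uncontrolled trials are less valid than those of RCTs, and leaves efficacy to an RCT. Efficacy is only a secondary objective, no efficacy test is planned, and an estimate with a 95% CI is already the planned report. All of this stands. However, the caveat never withdraws the use stated in the Aims, so the two sections remain at odds.

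A reader might infer that the protocol admits its estimate is inflated, or that the next trial will be undersized. The documents support neither. The Discussion's verbs are *can* and *may*. The Aims say only that the estimate will inform a calculation, and the SD of the change would do that harmlessly. A shortfall needs two further premises: the mean change becomes the target difference, and part of it is non-specific. At f = 0 there is no shortfall.

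Three limits on the numbers also stand:

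- The entry threshold is low, at least one episode in the past month, so regression to the mean may be modest. The article gives no score distribution from which to size it.
- The figures assume an RCT analysed on change scores. With baseline adjustment and equal variances at both times, n is multiplied by (1 + r)/2, where r is the baseline to week-12 correlation. For r from 0.3 to 0.7, 64 becomes about 64 × 0.65 = 42 to 64 × 0.85 = 54.
- No RCT size is planned, so no multiple of a planned size can be claimed.

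**Conclusion.** The point holds as a mismatch between a stated objective and the design. The Aims promise an efficacy estimate for sizing, the design yields an uncontrolled completers-only change that does not identify the difference from control, and the Discussion's caution does not resolve this. It affects neither the primary feasibility outcomes nor the sample size of 36.

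The effect on a future RCT is conditional. If the mean change were taken as the target difference and 25%, 50% or 75% of it were non-specific, power would fall from 80% to about 56%, 29% or 11%. Those shares and the standardised change of 0.5 are assumptions, and the article offers nothing from which to estimate them. Apart from bias, about 29 completers leave the assumed change with a 95% CI of 0.11 to 0.88, too wide to size a trial on.

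**What to change.** Reconcile the Aims with the limitations in the Discussion by rewording the secondary objective, for example: *to estimate the standard deviation of the Eating Loss of Control Scale score and of its change, with confidence intervals, the correlation between baseline and week 12, and retention, to inform a future sample size calculation.*

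In the Statistical analysis section, add that the mean change and its 95% CI are descriptive and will not be used as the between-arm target difference, which will be justified separately when the RCT is designed. This protocol need not prescribe how that later justification is made.

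The cost is a change of wording in two sections, with no new data, assessments or participants. The downside is that the pilot can no longer be cited as an estimate of NAC's efficacy.

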## Methods/design

### Design

This is an open-label single-arm pilot study to examine the feasibility of recruiting and retaining participants during a 12-week NAC intervention in people with loss of control eating. After completing the baseline assessments, all participants will receive NAC orally at a daily dose of 2400 mg (two capsules of 600 mg, twice daily) for 12 weeks. A follow up assessment will be conducted after treatment using the same measures as in the baseline assessment. The trial flow diagram (Fig. 1) depicts the overall procedure in the study. This single-site study will be conducted at the Florey Institute of Neuroscience and Mental Health, Melbourne, Victoria, Australia.

